## **Sensitivity analyses**

Sensitivity analyses will entail assessment of intervention effects for variables with high levels of missingness that were not included in the main analysis. We will explore the analyses including these variables without any imputation as well as imputing extreme values (e.g., all “yes” or all “no” responses missing values) to assess the degree which this influences our inferences for the intervention effectiveness. We will explore alternate specifications for the intervention variable where we assume the maximal intervention effect will be quicker (i.e., 3 months) or longer (i.e., 9 months). We will also explore whether treating period as an ordered variable and whether using visit date (as opposed to period) better describes the data.

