#### Analysis

The analytic strategy for TEC will be focused on assessing the effectiveness of the PCC intervention by comparing the PCC intervention group to the control group. The unit of randomization is healthcare facility and the unit of analysis is the individual. To test the effectiveness of the

intervention, we will use a standard stepped-wedge analytic approach (Hussey & Hughes, 2007) based on a generalized linear mixed model (GLMM) where facility is included as a random effect and period is included as a fixed categorical variable to adjust for secular trends. Due to a ramp up in intervention effect, we will determine code three different groups for the intervention analysis (control, early intervention ( $\leq 6$  months), late intervention ( $> 6$  months), fit as separate categories or ordered (Hughes et al., 2015; Kenny et al., 2021)). This decision is based on contextual experience in the facilities and anticipation that there will be a lag in seeing the benefits from training, mentoring, and data feedback (e.g., the first data feedback only occurred 3 months into the intervention). Furthermore, we will explore alternative parameterizations for secular trends including linear and cubic splines. If these alternative parameterizations better describe variability in the data (as determined by standard model fit statistics such as Akaike's Information Criterion [AIC]) then the model will be updated to reflect this accordingly. Distributions and link functions used will depend on the outcome (see outcome-specific sections below for more details).

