We will also include the following variables in our statistical models as they are thought to be causally related to the outcomes: age at enrollment, sex, in-care status, randomization strata (initial cluster randomization stratified by facility size and viral load coverage based on programmatic data). We will consider including the following potential confounders due to imbalance in randomization: time in care, WHO severity groups, marital status and education. We will use Fisher's exact tests, t-tests, and Wilcoxon rank-sum tests, as appropriate. Variables that exhibit some evidence of a difference between groups ( $P < 0.10$ ) will be included in the final statistical models. In the event that any of these variables have strong associations with the intervention groups but have high levels of missingness (e.g.,  $> 10\%$ ) then those variables will be excluded from the main analysis and will be further explored using sensitivity analyses (for more details see sensitivity analysis section below). We will use standard model diagnostic procedures and consider alternate specifications as needed if we face challenges with standard statistical issues such as model convergence or overfitting.

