## Sample size estimation

Assuming that 65% of individuals reported a positive patient experience at baseline and a very conservative intraclass correlation between facilities of 0.2, we estimated that we would be able to detect a 15.0% difference between intervention and control arms with 80% power and at  $p < 0.05$ .

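### Filling every missing value of an excluded TEC covariate with one extreme does not bound the intervention effect; with similar missingness across conditions, both fills stay confounded in the same direction

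*Combined protocol and SAP*

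**What the plan says.** SAP 4.0 (Patient Experience), Analysis, always includes age, sex, in-care status and randomization strata. It then adds a second tier: "We will consider including the following potential confounders due to imbalance in randomization: time in care, WHO severity groups, marital status and education". Second-tier variables that differ between groups at P < 0.10 enter the final model, with one exception: "In the event that any of these variables have strong associations with the intervention groups but have high levels of missingness" (above 10% is given as an example), "then those variables will be excluded from the main analysis and will be further explored using sensitivity analyses".

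The Sensitivity analyses paragraph of the same section takes these variables up: "Sensitivity analyses will entail assessment of intervention effects for variables with high levels of missingness that were not included in the main analysis". Two methods are named: "We will explore the analyses including these variables without any imputation as well as imputing extreme values". The example given for the second is to set the missing values all to yes or all to no. The stated aim is to see how far this changes the inference about effectiveness. For these covariates the paragraph gives no multiple imputation, no assumption about why values are missing, and no fill that differs by condition.

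**The concern.** A covariate that differs strongly between intervention and control surveys is a candidate for confounding, so the analysis that replaces adjustment in the main model has to be informative. Filling all missing values with the worst and then the best value is a familiar device for missing outcomes, where the two results can bracket the answer. A missing confounder behaves differently. Whichever extreme is used, the same people lose their true value, so adjustment is partial both times. Two results that agree with each other can then both be wrong by a similar amount and in the same direction.

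The extremes are also undefined for the variables concerned. Time in care, WHO severity group, marital status and education do not take the values yes and no, so the fill would have to be chosen at analysis.

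**Working it through.** The point concerns a rule, so there is no plan figure to reproduce. The check asks how much confounding remains after adjusting for a filled-in confounder.

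**Inputs from the documents**
- Share of surveys under intervention, from the first row of Table S5: (255 + 230)/(676 + 255 + 230) = 485/1161 ≈ 0.42. It is used only as a weight, with early and late intervention pooled.
- True effect for illustration: 0.15, the TEC design difference ("detect a 15.0% difference between intervention and control arms with 80% power").

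**Assumed, not in the documents**
- Binary confounder U with prevalence p = 0.4 under control and 0.6 under intervention, worth 0.20 on the outcome.
- Missing fraction m from 10% to 40%, unrelated to U within condition unless stated.

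**Formula.** Let U* be the filled-in U. In a linear (risk-difference or sum-score) model, the share of crude confounding left is

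S = 1 − b × [E(U*|intervention) − E(U*|control)] / (0.6 − 0.4),

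where b is the within-condition covariance of U and U* divided by the within-condition variance of U*, each averaged with weights 0.58 and 0.42. The mean of U* is p(1−m) for all-no and m + (1−m)p for all-yes. The covariance is p(1−p)(1−m) for both. The variance is mean × (1 − mean).

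**25% missing in both conditions.** The covariance is 0.24 × 0.75 = 0.18. The means of U* differ by 0.75 × 0.2, so S = 1 − 0.75b.
- All-no: means 0.30 and 0.45; variance 0.58 × 0.21 + 0.42 × 0.2475 = 0.2258; b = 0.797; S = 0.40.
- All-yes: means 0.55 and 0.70; variance 0.58 × 0.2475 + 0.42 × 0.21 = 0.2318; b = 0.777; S = 0.42.

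On the effect scale, leaving U out gives 0.15 + 0.20 × 0.2 = 0.19. The fills give 0.15 + 0.04 × 0.40 = 0.166 and 0.15 + 0.04 × 0.42 = 0.167. The true 0.15 lies outside that range.

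**Other equal-missingness cases (share left)**

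| Case | All-no | All-yes |
|---|---|---|
| 10% missing | 18% | 19% |
| 20% missing | 34% | 35% |
| 30% missing | 46% | 48% |
| 10% missing if U = 0, 30% if U = 1 | 46% | 19% |
| U at 0.2 vs 0.4, 20% missing | 27% | 48% |
| Continuous U, means 0.4 SD apart, 20% missing, filled at ∓3 SD | 74% | 69% |

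(In the last row, all-no means the low fill and all-yes the high fill.)

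**When the direction is shared.** Let m0 and m1 be the missing fractions under control and intervention. Under all-no, everyone with U* = 1 truly has U = 1, so confounding survives only among U* = 0. There the odds of U = 1 are p·m/(1−p), and the intervention-to-control ratio of these odds is OR × m1/m0. Under all-yes the corresponding ratio, among U* = 1, is OR × m0/m1. Both exceed 1 only if m1/m0 lies between 1/OR and OR. Here OR = (0.6/0.4)/(0.4/0.6) = 2.25.

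**Outside that range: 10% missing under control, 30% under intervention (ratio 3).** The covariance is 0.58 × 0.216 + 0.42 × 0.168 = 0.1958.
- All-no: means 0.36 and 0.42; variance 0.2359; b = 0.830; S = 1 − 0.830 × 0.06/0.2 = +0.75; estimate 0.180.
- All-yes: means 0.46 and 0.72; variance 0.2287; b = 0.856; S = 1 − 0.856 × 0.26/0.2 = −0.11; estimate 0.145.

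These fall on opposite sides of 0.15.

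**Check on the stepped-wedge layout.** The TEC survey population cells were multiplied by 4, with facility and period effects (facility fitted as fixed, which approximates the planned random effect), a continuous outcome, and 120 runs per row. The Monte Carlo SE is about 0.002.

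| Missing, control / intervention | U omitted | Full data | Complete case | All-no | All-yes |
|---|---|---|---|---|---|
| 20% / 20% | 0.184 | 0.145 | 0.143 | 0.158 | 0.159 |
| 10% / 30% | 0.189 | 0.149 | 0.148 | 0.179 | 0.144 |
| 30% / 10% | 0.188 | 0.148 | 0.147 | 0.143 | 0.179 |

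The complete-case fit tracks the full-data fit throughout; missingness was unrelated to outcome given condition. Its price is precision. In a separate linear simulation without clustering (679 control and 486 intervention surveys, 25% missing), the SE rose from 0.125 to 0.145, a factor of 1.16.

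**The case against.** Five arguments on the other side carry weight.

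- **The plan never calls the extremes a bound.** True; it uses them to judge influence. But two same-extreme fills cannot show the range of results the missing values allow.
- **The sound check is in the same sentence.** The complete-case refit did well in every simulated pattern. This stands and limits the harm. What remains is that a shift from the main result could come from adjustment or from dropping more than 10% of surveys.
- **The fills would still signal trouble.** A reader might infer that the check will look reassuring when the main estimate is confounded. The figures do not support that: at 25% missing the fills remove about 60% of the crude confounding, so the estimate moves clearly away from the unadjusted one. Only their agreement with each other misleads.
- **Yes and no may refer to the survey items.** The 12 TEC questions are dichotomous, and the wording is loose. However, the paragraph opens by limiting itself to variables left out of the main analysis for missingness, and the Analysis section sends the covariates there.
- **The trigger is association with group only.** Bias also needs association with outcome, which the rule does not establish.

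A reader might also infer that both extremes always err in the same direction. They do not: the 10%/30% case straddles the truth. Nor do the documents show that the reported TEC estimates are confounded.

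**Conclusion.** The point holds in a limited form. Filling every missing value of an excluded confounder with one extreme does not bound the intervention effect. With similar missing rates across conditions, both fills leave part of the confounding in the same direction: about 40% of it at 25% missing for a binary confounder at 0.4 versus 0.6. When the ratio of missing rates falls outside the confounder-intervention odds ratio, the fills can land on either side of the truth. An analyst without the true values cannot tell from the two results alone which case applies. The fill is also undefined for the four named covariates.

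The sizes rest on the assumed prevalences, confounder effect and missing fractions, and on a linear model with two conditions. The documents give no covariate missingness, so whether the rule is triggered is unknown. TEC is a secondary outcome and a usable complete-case refit is already planned. This is a cheap improvement, not a threat to the trial's conclusions.

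**What to change.** In SAP 4.0, Sensitivity analyses, delete the extreme-value imputation for covariates. For any covariate excluded from the main TEC model for missingness, specify instead:

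1. Multiple imputation, with outcome, condition (control, early, late), period, facility and the other covariates in the imputation model. Report the adjusted estimate beside the main result.
2. The model with and without the covariate on the same complete-case surveys, so that the effect of adjustment is separated from the change of sample.
3. A delta-adjusted imputation to test the missing-at-random assumption.

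Report covariate missingness by condition and whether the rule was triggered. If the yes/no fill was meant for missing survey items, say so and confine it to them.

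This does not require every selected covariate to stay in the main model whatever its missingness. That is debatable, because these covariates are chosen after the data are seen, at P < 0.10. A smaller repair is to fill with opposite extremes by condition. In the worked example (0.4 versus 0.6, equal missingness) this gave 0.126 to 0.196 at 20% missing, which contains the true 0.15, but the interval is wide.

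The cost is SAP wording, somewhat more analysis work (the imputation must respect facility clustering and serve the single items, sum score and PCA scores), and a missing-at-random assumption, which step 3 examines.

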## Sample size estimation

Assuming that 65% of individuals reported a positive patient experience at baseline and a very conservative intraclass correlation between facilities of 0.2, we estimated that we would be able to detect a 15.0% difference between intervention and control arms with 80% power and at  $p < 0.05$ .

## 5.0 – Secondary Outcome – Retention in Care

### 5.1 – In Care at 15 months

**Outcome:** This secondary outcome for retention is being in care at 15 months which will be defined as not being more than 30 days late to a visit at 15 months. We will use EHR data (i.e., SmartCare) that includes sociodemographic, clinical, visit history, and pharmacy data to determine this outcome.

**Population:** The population for this outcome will include all individuals ( $\geq 18$  years old) who made a visit to one of the Wave 1 or Wave 4 study facilities in the first 6 months of the 24-month study period (i.e., period 1). We restrict to facilities in wave 1 and 4 in order to allow a minimum of 15 months of exposure to either the intervention or control conditions at the time out outcome assessment without crossover. This allows us to analyze this aim like a parallel cluster-randomized trial.

|                   | Period 1                                                                                   | Period 2 | Period 3                     | Period 4 | Totals per wave |
|-------------------|--------------------------------------------------------------------------------------------|----------|------------------------------|----------|-----------------|
| Wave 1            | Intervention
All individuals making visit to Facility during Period 1
~40,000 |          | Outcome Ascertainment |          | ~40,000         |
| Wave 2            |                                                                                            |          |                              |          |                 |
| Wave 3            |                                                                                            |          |                              |          |                 |
| Wave 4            | Control
All individuals making visit to Facility during Period 1
~40,000      |          | Outcome Ascertainment |          | ~40,000         |
| Totals per period | ~80,000                                                                                    |          |                              |          | ~80,000         |

**Analysis:** Time zero will be the first visit a participant makes at a study facility during Period 1. Individuals will be considered to be in care if they are not more than 30 days late at the 15-month time point. We will use mixed effects logistic regression, accounting for clustering at the facility-level using random effects. The main exposure will be exposure to the PCC intervention. To account for potential imbalances due to cluster randomization at baseline and also increase precision, we will adjust for individuals' care status at enrollment (in care, new ART, LTFU), sex, age, time in care, baseline clinic-level retention (i.e., percent of visits where patient was more than 30 days late to their next appointment assessed in the 6 months prior to study start), and randomization strata (initial cluster randomization stratified by facility size and viral load coverage based on programmatic data). Facility will be included as a random effect. We will consider including the following potential

confounders due to imbalance in randomization: WHO severity groups, marital status, and education. We will use standard model diagnostic procedures and consider alternate specifications as needed if we face challenges with standard statistical issues such as model convergence or overfitting. We will use marginal estimation commands to report absolute and relative risk differences under treatment versus control conditions.

In addition to the overall analysis, we will perform stratified analyses to assess changes specifically across:

- Care Status (in care, new ART, LTFU)
- Sex
- Age (<25, 25-44, >45)
- Advanced HIV Disease at enrollment in care (WHO Stage 3 or 4, CD4<200) – Dependent on adequate coverage of CD4 measurements
- Clinic Size and Type
- We may assess composite subgroups of age, sex, and care status (e.g., Male <25 years old, LTFU not suppressed at baseline) if amenable based on sample sizes. We will not perform analyses with less than 500 participants.

**Sensitivity Analysis:** We will perform several sensitivity analyses to ensure the robustness of our results by exploring an alternative definition of 90 days late at the 15-month time point.

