|                  | Control
(N=73) | Intervention
(N=77) |
|------------------|---------------------------|--------------------------------|
|                  | n (%)                     | n (%)                          |
| Definite Failure | 14 (19·2)                 | 16 (20·8)                      |
| Probable Failure | 32 (43·8)                 | 27 (35·1)                      |
| Probable Success | 27 (37·0)                 | 34 (44·2)                      |
| Definite Success | 0 (0)                     | 0 (0)                          |

Chi-square test:  $p=0\cdot53$

| Table S11. Deaths, Silent Transfers, and Official Transfers by PCC intervention status in Cohort 4 (N=933) |                            |                                 |          |
|-------------------------------------------------------------------------------------------------------------------|----------------------------|---------------------------------|----------|
|                                                                                                                   | Control
(n=453) | Intervention
(n=480) | p-value* |
|                                                                                                                   | n (%)                      | n (%)                           |          |
| Total Cohort (n=933)                                                                                       |                            |                                 |          |
| Died                                                                                                              | 4 (0·9)                    | 10 (2·1)                        | 0·132    |
| Silent Transfer                                                                                                   | 16 (3·5)                   | 7 (1·5)                         | 0·041    |
| Official Transfer                                                                                                 | 35 (7·7)                   | 39 (8·1)                        | 0·82     |
|                                                                                                                   |                            |                                 |          |

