## **5.0 RESEARCH AIM**

Although the evolution of health systems toward decentralization and now differentiated models of care have extended the reach of HIV services, treatment outcomes are still far from uniformly successful. Even though few patients stop care permanently, lapses in care from weeks to months are still common (i.e., patients are inconsistently in care), and some settings lapses in treatment likely reaches nearly 50% after three years. In addition, even though retention in the system is higher than retention in a particular clinic, recent analyses suggest that patients who have undocumented transfers between facilities (“silently transfer”) are up to five-fold more likely to be viremic than patients at their original clinics (45). While large-scale population based surveys in Africa suggest that 85% or more of patients on treatment are suppressed, these figures do not necessarily take into account those who have been on treatment in the past but who have now lapsed, which could influence estimates considerably (46).

Furthermore, recent research work in Zambia done by this group suggests that looking nationally or even regionally hides important variation in the magnitude and types of barriers to care across facilities. We found, for example, that mortality rates, even after adjusting for CD4 levels ranged from 2% to 20%, and that lapses in retention varied from 5% to 40% by two years (2,47). When lost, patients were sought in the community and surveyed, their reasons for stopping care reflected a great deal of variability. In some facilities, transportation problems were paramount, while in others psychosocial problems (such as stigma and depression) were prevalent (and transportation problems were uncommon)(3,48,49). This across-facility variability in both the magnitude and the nature of service delivery problems leads to our scientific premise: if problems with performance are site specific, then the intensity and nature of the intervention should be targeted to the measured problems at each site.

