#### 8.7.1.2 Full cohort-for retention in care

We will, nevertheless, also assess endpoints on the entire clinic based cohort represented in the EMR, using outcomes that can be assessed in the electronic medical record, specifically retention using visits, transfer and passively collected vital status. Since all patients who experience an encounter during the 24-month study period will be examined for the retention endpoint, which we anticipate based on current program data to be-as many as 170,000. We seek a waiver of consent for measurement of clinical care and outcome data in this

cohort. Reviewing patient outcomes as recorded in routine medical records is of minimal risk. It is not possible to seek written consent from the entire cohort of patients. We will treat known deaths as lapses in treatment.

Figure 1

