#### *8.7.2.1 Measurements for Retention*

For analyses using the full cohort of individuals in the EMR, we will assess retention using appointment and visits as recorded in the EMR.

### 8.8 Analysis for Objective 3

The primary outcome for objective 3 is treatment success 15 months after initial visit during period 1 of the study. For the analysis of this primary outcome we will assess the fraction with treatment success or not at 15 months using logistic regression. Random effects will be used to address within site correlation. Adjustment will be made for composition of the cohort recruited, in particular for age, sex, and time on ART at first visit during the study period. Sensitivity analyses for the primary analysis will include altering interval of absence considered a failure, and classifying all transfers out as either successes or failures.

For retention, we will calculate the cumulative incidence of a missed visit by 30 or more days at up until 15 months of follow-up time. We will use the Kaplan Meier approach, stratified by the intervention with a log rank test for significance. We will explore competing risks for transfers and mortality if those outcomes are not trivial in magnitude. In additional analyses we will use a multivariable regression, starting with Cox proportional hazards model if assumptions about data are met, to assess the effect of the intervention on retention. We will address clustering by site with a random effect term. In secondary analysis, we will adjust for facility and patient characteristics. If data are prevalent, we will consider the use of inverse probability weights or imputation to address missing outcomes.

### 8.9 Design of Objective 4

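### The 15-month retention outcome in SAP 5.1 has no rule for patients who transfer, so it mixes staying in HIV care with staying at the enrolling clinic

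*Combined protocol and SAP*

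**What the plan says.** SAP section 5.1 gives this definition: "This secondary outcome for retention is being in care at 15 months which will be defined as not being more than 30 days late". The data source is the routine record: "We will use EHR data (i.e., SmartCare) that includes sociodemographic, clinical, visit history, and pharmacy data to determine this outcome". That list does not mention transfer status. The analysis paragraph repeats the 30-day rule without adding to it. The only sensitivity analysis is "exploring an alternative definition of 90 days late at the 15-month time point".

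The protocol is more explicit. Section 8.7.1.2 says the full EMR cohort would be assessed on "specifically retention using visits, transfer and passively collected vital status". Section 8.8 says that competing risks for transfers and deaths would be explored in the retention analysis unless trivial in size. For the primary outcome, the same section plans "classifying all transfers out as either successes or failures" as a sensitivity analysis. Section 5.0 states the underlying problem: "retention in the system is higher than retention in a particular clinic".

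**The concern.** A patient who moves to another clinic stops attending at the first one. Under a rule based only on lateness, that patient appears more than 30 days late at 15 months. Moving the threshold to 90 days does not change this, because someone who has left is late at both. The rule therefore scores some people who are on treatment elsewhere as out of care.

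Two quantities are then combined: remaining in HIV care, and remaining at the enrolling clinic. A better clinic experience could affect the second without affecting the first to the same degree. If moves are equally common in both arms, the absolute difference is little affected. If they are more common in control, the estimate is larger than the effect on being in care anywhere. The reported lower confidence limit is only 0.6 points above zero, so a small differential could matter for the conclusion.

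**Working it through.** **Inputs**

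- Table S11 (Cohort 4; 453 control, 480 intervention): silent transfers 16 and 7, official transfers 35 and 39, with chi-square p-values 0.041 and 0.82.
- Table S8: adjusted retention difference 5.9 points, 95% CI 0.6 to 11.2. Figure S1 identifies the EHR retention population as Cohort 3.
- SAP section 3.0: Cohort 4 is drawn by care-status quota and excludes people planning to move away.

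**Step 1: reproduce the plan's figures.** Silent transfers are 16/453 = 3.53% and 7/480 = 1.46%, a gap of 2.07 points. The pooled proportion is 23/933 = 2.465%. The pooled standard error is √[0.02465 × 0.97535 × (1/453 + 1/480)] = 1.016 points, so z = 2.07/1.016 = 2.04 and p = 0.041, as stated. Official transfers are 35/453 = 7.73% and 39/480 = 8.12%, a gap of -0.40 points with p = 0.82, as stated.

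**Step 2: how common are transfers?** 16 + 7 + 35 + 39 = 97, and 97/933 = 10.4%. Of the 23 silent transfers, 15 + 7 = 22 had no endline viral load, against 11 + 10 = 21 of the 74 official ones. This suggests, without proving, that care after a silent transfer was mostly not visible in the record.

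**Step 3: how firm is the gap between arms?**

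- Silent transfers: 2.07 points, unclustered 95% CI 0.06 to 4.08. Fisher's exact p = 0.056; continuity-corrected p = 0.067.
- Clustering: Table S11 uses an ordinary chi-square test, but the data come from 16 facilities averaging 933/16 = 58.3 patients. The documents give no ICC for transfers, so a range is assumed. Dividing the chi-square by 1 + 57.3 × ICC gives p of about 0.07, 0.10, 0.16 and 0.30 at ICCs of 0.005, 0.01, 0.02 and 0.05. At 0.2, the value the SAP uses to size the primary outcome, p is 0.56.
- All transfers: 51/453 = 11.26% against 46/480 = 9.58%, a gap of 1.67 points (CI -2.25 to 5.60), p = 0.40.

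**Step 4: what would this do to the retention effect?** Assume that the transfers in question were all scored out of care, that they should count as in care, and that the Cohort 4 gap applies in Cohort 3. The corrected difference is 5.9 minus the differential, with both limits shifted by the same amount.

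| Differential (points) | Estimate | 95% CI, shift taken as fixed |
|---|---|---|
| 0 (Table S8 as reported) | 5.9 | 0.6 to 11.2 |
| 0.06 (lower limit of silent gap) | 5.84 | 0.54 to 11.14 |
| 0.6 | 5.3 | 0.0 to 10.6 |
| 1.67 (all transfers) | 4.23 | -1.07 to 9.53 |
| 2.07 (silent transfers) | 3.83 | -1.47 to 9.13 |
| 4.08 (upper limit of silent gap) | 1.82 | -3.48 to 7.12 |
| 5.9 | 0.0 | -5.3 to 5.3 |

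Adding the unclustered sampling error of the silent-transfer gap: the SE of 5.9 is (11.2 - 0.6)/3.92 = 2.70, the SE of the gap is 1.03, and √(2.70² + 1.03²) = 2.89. The interval around 3.83 becomes about -1.8 to 9.5.

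A differential of 0.6 points, or 0.6/2.07 = 29% of the observed gap, brings the lower limit to zero. Removing the whole estimate would take 5.9 points, nearly three times the observed gap.

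**The case against.** A reader might infer that the outcome counts every mover as out of care and that the retention effect is therefore biased towards the intervention. The documents do not support that, for four reasons.

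- **The rule is not stated.** The SAP is silent on transfers. The protocol lists transfer as an EMR item, so official transfers (74 of the 97) may have been handled separately. Nothing says whether SmartCare shows visits at another facility.
- **The differential is not established.** Official transfers are balanced, and the gap for all transfers has p = 0.40. The directional case rests on 16 against 7 silent transfers and a p-value that does not survive Fisher's test or modest clustering.
- **Carrying the gap over is an assumption.** The calculation sets a crude Cohort 4 gap against an adjusted Cohort 3 effect. Cohort 4 took a quarter new on ART, a quarter lost or late and half in care. In Table S13, the nearest EHR figure, 805,353 of 1,009,352 visits (80%) were by patients in care.
- **Fewer silent transfers may itself be a benefit.** Protocol section 5.0 reports that silent transferrers are more often viremic. Retention at the enrolling clinic is a legitimate target, and under it counting movers as not retained is correct.

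It is also tempting to recode transfers within Table S9 (375/453 against 400/480 retained) and read off a reversed sign. That table does not say how transfers were scored or whether tracing was used. Also, 74 - 21 = 53 of the official transfers had an endline viral load, so they cannot simply be placed among the not retained.

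The departure from the protocol is narrower than it looks. The competing-risk clause belonged to the time-to-event analysis; the Figure S6 legend explains why missed visits moved to logistic regression. The transfer sensitivity analysis was written for the primary outcome.

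All of this stands against a finding of bias. None of it supplies the missing rule or says which kind of retention is being estimated.

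**Conclusion.** The point holds as a gap in definition with a possible consequence for the result. SAP 5.1 does not say how official or silent transfers are classified, and its single sensitivity analysis cannot address them. The estimate therefore mixes retention in HIV care with retention at the enrolling clinic.

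As a measure of being in care anywhere, 5.9 points may be too high. If the silent-transfer gap carried over in full, the figure would be about 3.8 (about -1.5 to 9.1). That rests on the Step 4 assumptions, none of which the documents confirm. What can be said firmly is that the interval's exclusion of zero depends on an unstated rule, since a 0.6-point differential is enough to bring the lower limit to zero. Whether the effect is overstated, and by how much, is not shown.

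The same question could be asked of the missed-visit outcome in SAP 5.2, but the documents give no figures from which to size it, so no claim is made there. This is a cheap improvement.

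**What to change.** In SAP section 5.1:

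1. Label the lateness-only result *retention at the enrolling facility*, and state whether that or retention in care anywhere is the target.
2. Use the EHR transfer field. For documented transfers-out of patients not already more than 30 days late at transfer, report the effect with them counted as in care, counted as out of care, and excluded or treated as a competing event. All are needed, because scoring a transfer-out as in care assumes that the patient arrived and stayed in care.
3. Add a sensitivity or tipping-point analysis for silent transfers, using arm-level tracing rates from the sub-cohort and carrying their sampling error and the clustering by facility. Splitting further by care status is not practical: 23 events over two arms and three care-status groups is about four per cell.

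The cost is some SAP wording and a modest amount of extra analysis on data that should already be held (the EHR transfer field and the sub-cohort tracing). The retention effect may shrink, and its interval will be wider where the tracing rates are used.
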